#### Measurement Tools

Measurement tools in the cohort study (WP1) and the RCT (WP4) include self-report questionnaires, PHQ-9, the Generalized Anxiety Disorder scale [30], the Flourishing Scale [31], the Children’s Somatic Symptoms Inventory 8 [32], and single variables to determine participants’ familiarity with, use of, and satisfaction with digital services, as well as their perspectives on service providers’ cultural and linguistic competence and youths’ preferences regarding continuity and confidentiality in care.

#### Safety Considerations

The project includes several measures to ensure participant safety and well-being. Participants who may need support during the study are encouraged to contact established health care services, including school health professionals, general practitioners, and mental health helplines, with emergency services available for urgent situations. The project also includes culturally sensitive communication and interview procedures to reduce the risk of misunderstanding or harm.

#### Data Safety

All personal data collected are handled in accordance with strict privacy regulations. Data are used solely for the purposes outlined in the study, and participants’ confidentiality is safeguarded throughout. Participants also retain the right to access, correct, or delete their personal information and to file complaints with the Data Protection Authority if they have concerns about data processing. All sensitive data are securely stored on a dedicated server. These measures ensure that the research is responsive to participants’ needs and conducted with appropriate protections.

### Statistical Considerations and Data Analysis

#### Sample Size Calculation

Approximately 25% of youth are expected to experience mild to moderately severe symptoms of depression (PHQ-9 scores of 5‐19) [9,12,47]. To ensure a sufficient number of eligible participants for the RCT (WP4), a population cohort of 1500 youth will be recruited. This cohort size is designed to provide an adequate number of individuals who meet the inclusion criteria, which are scores of mild to moderately severe range on the PHQ-9, and to account for potential exclusions due to eligibility, nonconsent, or attrition. On the basis of an anticipated 20% dropout rate, 80% statistical power, a significance level of 0.05, and a moderate effect size of 0.35 (Cohen *d*), with equal allocation between intervention and control groups, the required sample size for the RCT is estimated to be 294. This has been rounded up to 300 to maintain sufficient power and accommodate potential variability.

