### Study Population

Throughout all phases of the project, participants will be recruited among youth who identify as belonging to at least one of the following groups: national minorities (Forest Finns, Jews, Kven or Norwegian Finns, Roma, and Romani), Indigenous Sámi youth, and refugees. In addition, in the first 2 of 3 cohort surveys (WP1), youth not belonging to the mentioned minority groups will be included. The inclusion of the broader group of youth will enable comparisons between minority and nonminority youth. During the co-design phase (WP3), professionals working in health and social services who engage directly with these youth groups will also be recruited.

In WP1, up to 1500 youth with minority backgrounds will be recruited for each of the 3 cohort surveys. Additionally, the first 2 cohort surveys will include up to 1500 youth who do not identify as belonging to the described minority groups. WP2 will include 50 to 100 youth from the different minority groups, ensuring representation across all groups. WP3 will involve a minimum of 50 youth and professionals. WP4 will recruit approximately 300 youth from the WP1 cohort for an RCT and 25 to 45 youth for a qualitative study based on their exposure to the adapted digital services, regardless of RCT participation.

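### The trial size of 294, rounded to 300, does not follow from its stated inputs: they require about 325, and 300 gives about 77% power rather than 80%

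*Protocol article*

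**What the plan says.** The Sample Size Calculation section of the protocol article lists its inputs in one sentence:

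- dropout: "On the basis of an anticipated 20% dropout rate"
- power: "80% statistical power"
- alpha: "a significance level of 0.05", with no statement of one- or two-sided
- effect: "a moderate effect size of 0.35", given as Cohen d
- allocation: "with equal allocation between intervention and control groups"

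From these it concludes that "the required sample size for the RCT is estimated to be 294". It then adds: "This has been rounded up to 300 to maintain sufficient power and accommodate potential variability". The Study Population section carries the rounded figure forward: "WP4 will recruit approximately 300 youth from the WP1 cohort for an RCT".

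The endpoint being sized is the PHQ-9 score at 12 months, compared between two arms (Study Outcomes; Data Analysis). The sample-size paragraph mentions no baseline adjustment or other variance reduction. For the trial comparison, the Data Analysis section names an intention-to-treat analysis and an instrumental variables analysis, but no covariate-adjusted model.

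**The concern.** All the inputs needed for a standard two-sample calculation are given, so a reader should be able to reproduce the result. For d = 0.35 at 80% power, the number of evaluable participants alone is close to 260. Allowing for 20% dropout must then take the total well above 300, yet the stated total is below it.

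Study Outcomes describes the trial as the only component designed to evaluate effectiveness quantitatively, so this is the only power statement behind that evaluation. If the figure is wrong, the trial has less power than it claims, and a null result would be read against a power that the design does not have.

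**Working it through.** **Inputs**, all from Sample Size Calculation: d = 0.35, power 0.80, alpha 0.05, ratio 1:1, dropout 0.20. Two-sided testing is assumed by convention because the article does not say; one-sided is tried below.

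**Step 1. Evaluable participants per arm.** n = 2(z₀.₉₇₅ + z₀.₈₀)² / d² = 2(1.960 + 0.842)² / 0.1225 = 128.1, so 129. The t-test gives 129.1, so 130. Total evaluable: 258 or 260.

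**Step 2. Allow for dropout.** 258/0.80 = 322.5, so 323; 260/0.80 = 325. Rounding up within each arm adds one to either total.

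**Step 3. Try to reproduce 294 at the stated 80% power.**

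| Reading | Total |
|---|---|
| Two-sided, N/(1 − 0.20) | 323–325 |
| Two-sided, N × 1.20 (a common mistake) | 310–312 |
| Two-sided, no dropout allowance | 258–260 |
| One-sided, N/(1 − 0.20) | 253–255 |
| One-sided, N × 1.20 | 243–245 |

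None gives 294. The figure does appear for two-sided 85% power with no dropout: 2(1.960 + 1.036)² / 0.1225 = 146.6, so 147 per arm and 294 in total. One-sided 85% power with 20% dropout gives 295. Both contradict the stated 80% power, and the first also omits the stated dropout. Neither is evidence of how 294 was obtained.

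**Step 4. Power at the stated sizes** (two-sided, unadjusted, d = 0.35).

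| Randomised | Evaluable at 20% dropout | Power, t-test | Power, normal | Detectable d at 80% power, t-test |
|---|---|---|---|---|
| 294 | 235.2 | 76.2% | 76.5% | 0.367 |
| 300 | 240 | 77.0% | 77.4% | 0.363 |

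**Step 5. Shortfall.** Against 294: 323 − 294 = 29 to 325 − 294 = 31, about 9% of the requirement. Against 300: 23 to 25, about 7 to 8%. Put differently, 300 randomised keeps 80% power only if dropout is at most 1 − 258/300 = 14.0% (normal) or 1 − 260/300 = 13.3% (t-test), not 20%.

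**Step 6. Effect of adjusting for baseline PHQ-9.** With correlation r between baseline and 12 months, the required number is multiplied by (1 − r²). At 120 evaluable per arm, power is 80.8% for r = 0.30 and 87.7% for r = 0.50. By the normal formula, 240 evaluable reaches 80% power when 256.3(1 − r²) = 240, that is r of about 0.25.

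**Step 7. Could the cohort supply 325?** The section's own figures give 0.25 × 1500 = 375 eligible youth. Randomising 325 tolerates losses before randomisation of 1 − 325/375 = 13.3%; randomising 300 tolerates 20%.

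**The case against.** The strongest objection is that 77% is conditional on an analysis the article does not specify. Neither sidedness nor the test is given. A baseline PHQ-9 will exist, because the 6-month survey is the trial baseline. If the authors planned to adjust for it, one added assumption reproduces the figure exactly: 128.14 × (1 − 0.30²) = 116.6, so 117 per arm; 117/0.80 = 146.25, so 147 per arm and 294 in total. An article condenses a fuller protocol, so an unreported assumption is as compatible with 294 as a slip in arithmetic.

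Part of this stands. The 77% does rest on a two-sided, unadjusted comparison, and the origin of 294 cannot be known from the article. But the section presents 294 as the result of a listed set of inputs, and a correlation is not among them; none appears anywhere in the document. One-sided testing does not help: 240 evaluable would then give about 86% power, but the requirement would be 253 to 255, so 294 still would not follow.

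It is also fair that three power points is small, that d = 0.35 and 20% dropout are planning guesses, and that the trial size is described as approximate. This bears on how much harm the error does. It does not make the stated figure correct.

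**Conclusion.** The concern holds. On the stated inputs the requirement is 323 to 325 randomised, not 294, and no standard reading at 80% power recovers 294. That mismatch does not depend on sidedness.

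At the planned 300 with 20% dropout, power for d = 0.35 is 77.0% (77.4% by normal approximation), about 3 points below the stated 80%. This assumes a two-sided, unadjusted comparison. On the same assumption, the statement that 300 keeps sufficient power is not supported by the plan's own numbers. The deficit is modest, but the paragraph is wrong as written and should be corrected.

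**What to change.** Correct the Sample Size Calculation paragraph. State that the test is two-sided (or otherwise), and give 323 to 325 as the unadjusted requirement in place of 294. Then take one of two routes:

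- **(a)** Keep 300 and report what it delivers: 77% power for d = 0.35 after 20% dropout, or 80% power for d of about 0.36.
- **(b)** Keep 300 and base the power on a primary comparison adjusted for baseline PHQ-9, with the assumed correlation stated. A value of 0.30 gives 80.8% at 240 evaluable. Data Analysis should then name that adjusted model as the primary analysis. The correlation needs some justification, because eligibility restricts baseline PHQ-9 to 5–19, which tends to lower it. If 294 did come from such a calculation, say so and give the correlation.

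The cost is one reworded paragraph, plus a line in Data Analysis under (b), and either a slightly lower stated power or an explicit correlation assumption. Neither route needs more participants. Recruiting to 325 instead is possible on the article's own prevalence, but leaves room for only about 13% loss before randomisation.

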#### Participant Numbers in the Qualitative Phases

In the qualitative phases of the project (WP2 and the qualitative component of WP4), participant recruitment will be guided by the principle of *information power*, which posits that the number of participants should be determined by the richness, relevance, and sufficiency of the data in relation to the study objectives [43]. For planning purposes, the estimated number is 50 to 100 youth participants for WP2 and 25 to 45 participants for WP4. However, these estimates remain flexible and will be adjusted based on ongoing assessments of data adequacy in addressing the research questions. Recruitment will also be shaped by practical constraints, particularly the limited availability of participants from certain minority youth populations, which may impact the final participant numbers.

#### Data Analysis

Quantitative data analyses will be carried out for WP1 and WP4. In WP1, data analysis will include univariate analyses for descriptive statistics, whereas factors associated with service use will be assessed using correlation analyses, regression models, and multiple regression models to explore multiple predictors and adjust for confounders, for example, generalized linear models and linear and generalized additive models for nonlinear associations between predictor and outcome. Temporal changes will be assessed using mixed models to assess factors affecting service use.

To assess the use and acceptability of the intervention, that is, the adapted digital mental health services for youth, we will use data from the RCT to determine the proportion of participants who report using it. An intention-to-treat analysis will be used to test the effectiveness of the intervention offer, whereas an instrumental variables analysis will be applied to determine the effectiveness of the received intervention [48]. The primary outcome will be the PHQ-9 at 12 months of the trial. Subgroup analyses will be carried out for different minority groups. Results will provide data on variability in depression outcomes in the different groups. Safety will be assessed by determining the proportion of participants with deteriorated mental health status through higher PHQ-9 scores. Service satisfaction will be assessed using single-item questions, each targeting participants’ satisfaction with 1 of 8 different types of digital services. A cost-effectiveness analysis of the intervention for youth will be carried out by undertaking a cost-consequences analysis [49]. It will compare individuals taking advantage of the adapted services with those who do not. The analysis will take a societal perspective, relating costs associated with introducing the new interventions and attributable to youths’ mental health, school absence, and work productivity (if they are in work), as well as their quality of life.

Qualitative data analyses will be carried out in WP2 and the qualitative part of WP4. The data will be analyzed using qualitative content analysis [45] or similar types of analyses. Moreover, 2 mixed methods analyses will be conducted: the first will integrate qualitative data from WP2 with quantitative data from the cohort surveys in WP1, using triangulation to assess convergence, complementarity, and discrepancies [46]; the second will be carried out within WP4, combining data from the RCT and qualitative interviews to evaluate the implementation and impact of adapted digital services. The specific analytic approaches for both mixed methods analyses will be determined based on the nature and quality of the data collected, allowing for flexibility to ensure methodological rigor and relevance.

Data collected in WP3 will be analyzed using a thematic approach, drawing on principles of participatory and design-based research. Field notes and observations from the co-design workshops will be reviewed to identify recurring themes, patterns, and insights related to youth and professional perspectives on digital service adaptation. These qualitative data will be triangulated with findings from WP1 and WP2, as well as input gathered during youth seminars and project meetings, to ensure a comprehensive and contextually grounded analysis. The analysis will be iterative and collaborative, involving youth coresearchers throughout the process to ensure that interpretations reflect their lived experiences and priorities. This participatory approach supports the development of actionable recommendations that are both evidence-informed and aligned with the rights of youth, particularly those from minority backgrounds. The final recommendations will be synthesized and presented to service providers for consideration and potential implementation.

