## Introduction

### Background

Approximately 10% of youth worldwide are diagnosed with mental disorders [1]. There are mental health disparities among minority youth internationally, and these are affected by social determinants of health that are influenced by factors such as socioeconomic status, access to education and health care, and experiences of discrimination [2]. Youth from Indigenous and national minority groups have poorer mental health than the general population. For example, a systematic review found that Indigenous populations had suicide rates 20 times higher than non-Indigenous populations, with the highest rates in youth aged 15 to 24 years [3].

The Indigenous population in Norway is the Sámi. There is limited knowledge about the mental health of Sámi youth. During the period from 1970 to 1998, suicide rates among Sámi youth were twice those of the majority youth population in Norway [4]. Internationally, asylum-seeking and refugee youth have high rates of mental disorders, such as posttraumatic stress disorder, anxiety, and depression [5-8]. In Norway, up to 42% of asylum-seeking and refugee youth have been found to fulfill the criteria for psychiatric disorders [9]. A recent review reporting on the mental health of the Roma population in Europe found a higher proportion of mental disorders among children compared to the majority population and limited access to mental health care [10]. There is, however, no knowledge about the mental health among youth who belong to the following five national minority groups: Forrest Finns, Jews, Kven or Norwegian Finns, Roma, and Romani [11].

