### Inclusion and Exclusion Criteria

In WP1, WP2, and WP3, the inclusion criteria are youth aged 16 to 25 years who identify as belonging to at least one of the following groups: national minorities (Forest Finns, Jews, Kven or Norwegian Finns, Roma, and Romani), Indigenous Sámi youth, and refugees. The term “refugees” is used inclusively to refer to all youth who consider themselves to be refugees, regardless of their official status as defined by the national government. Moreover, the first 2 cohort surveys in WP1 also include youth aged 16 to 25 years who do not define themselves as belonging to any of these minority groups. WP3 also includes professionals working in health services, social services, and related sectors (eg, education) who engage directly with youth from minority backgrounds, as well as youth representatives aged 16 to 35 years who belong to any of the mentioned minority groups. Additional inclusion criteria for youth participating in the RCT in WP4 include a Patient Health Questionnaire (PHQ-9) score indicating mild to moderately severe depressive symptoms (scores from 5 to 19). Youth included in the qualitative study in WP4 are those who have been exposed to the adapted digital services. Youth aged <16 or >25 years are excluded from participation. Participants across all groups must provide written informed consent to take part in the research.

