### Study Outcomes

Given the nature of the *InvolveMENT* project, specific primary and secondary outcomes are defined for the RCT (WP4), which is the only component designed to evaluate the effectiveness of adapted digital mental health services quantitatively.WP2 and WP3 are exploratory and developmental in nature and therefore do not include predefined outcome measures. The primary outcome is the PHQ-9 score at 12 months of the trial. The secondary outcomes include scores for Generalized Anxiety Disorder [29,30], the Flourishing Scale [31], and the Children’s Somatic Symptoms Inventory 8 [32]. These outcomes are based on self-report and may be influenced by factors such as cultural, language, and social differences in diverse minority populations. While no single outcome measure has been validated, and culturally adapted tools are lacking across the included minority ethnic groups, these commonly used instruments have been selected as a choice to support knowledge generation in the absence of more inclusive and adapted alternatives. Service acceptability will be assessed by calculating the proportion of participants who use the adapted services.

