The evaluation study (WP4) will assess the implementation of recommendations developed in WP3 through two complementary procedures: an RCT and a qualitative study. The RCT will use the same survey instruments as WP1, with baseline data collected at the 6-month survey (before service adaptations) and follow-up data at the 18-month survey. The qualitative study will explore youth experiences with the adapted digital services, focusing on perceived support, safety, and satisfaction. Data will be collected through individual and focus group interviews depending on participants’ preferences. They will be conducted in participants’ preferred languages with professional interpreters as needed. Participants may include both RCT participants and others exposed to the adapted services. The number of participants will be guided by the concept of information power [43], with an estimated 25 to 45 participants. Interviews will be analyzed using qualitative content analysis [45], and findings will be integrated with RCT data through mixed methods analysis, applying triangulation to assess convergence, complementarity, and discrepancies [46].

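### The only quantitative safety endpoint is a higher PHQ-9 score, so individual worsening of anxiety or other measured domains without a PHQ-9 rise is not counted as harm

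*Protocol article*

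**What the plan says.** Objective 5 (Aim and Objectives) lists safety among the properties of the adapted services to be assessed. The Data Analysis section states how: "Safety will be assessed by determining the proportion of participants with deteriorated mental health status through higher PHQ-9 scores". It names no other scale, no single item and no adverse event for this purpose.

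The article elsewhere treats a PHQ-9 score as a summed score. The trial's eligibility criterion is a "score indicating mild to moderately severe depressive symptoms (scores from 5 to 19", and the recruitment and sample size sections use the same range.

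Other domains are measured. "Measurement tools in the cohort study (WP1) and the RCT (WP4) include self-report questionnaires, PHQ-9, the Generalized Anxiety Disorder scale", and the list goes on to the Flourishing Scale and the somatic symptoms inventory. "The RCT will use the same survey instruments as WP1, with baseline data collected at the 6-month survey", and follow-up is at the 18-month survey. In Study Outcomes these scales serve effectiveness: "The secondary outcomes include scores for Generalized Anxiety Disorder", followed by the flourishing and somatic scales.

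Safety also appears in the qualitative part: "The qualitative study will explore youth experiences with the adapted digital services, focusing on perceived support, safety, and satisfaction". An estimated 25 to 45 youth are to be interviewed, all of them exposed to the adapted services.

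**The concern.** The safety rule covers depression only, while the article's own account of the population is wider. The Background reports that "asylum-seeking and refugee youth have high rates of mental disorders, such as posttraumatic stress disorder, anxiety, and depression", and cites a review in which "Indigenous populations had suicide rates 20 times higher than non-Indigenous populations, with the highest rates in youth aged 15 to 24 years". It adds that suicide rates in Sámi youth were twice those of majority youth between 1970 and 1998.

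Under the stated rule, a youth who becomes more anxious while the PHQ-9 is unchanged or lower is counted as not deteriorated. If the adapted services relieve depressive symptoms on average, as the trial hopes, more of the youth who worsen elsewhere will fall into that group. At stake is the meaning of the safety statement: a similar proportion of PHQ-9 deterioration in the two arms says little about individual harm in domains that the rule does not look at.

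**Working it through.** No figure in the article bears on this point, so there is none to reproduce. The check is first a comparison of sections, then an illustration of size on assumed inputs.

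**1. What each source can show about individual harm, by arm**

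| Source | Domain | Both arms? | Counts individuals who worsened? |
|---|---|---|---|
| Safety sentence, Data Analysis | PHQ-9 | Yes | Yes |
| Secondary outcomes, Study Outcomes | Anxiety, flourishing, somatic symptoms | Yes | Not stated; scores only |
| Interviews, evaluation study | Perceived safety | No, exposed youth only | No |
| Safety Considerations | Signposting to services | Not an outcome | No |

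No row gives a between-arm count of deterioration outside the PHQ-9, although the data for one come from the same two surveys.

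**2. Anxiety: share of worsened youth not flagged (assumed inputs)**

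Let G and P be the changes in anxiety and PHQ-9 from the 6-month to the 18-month survey, each in units of its own SD of change. Assume they are bivariate normal with correlation r and a common mean m. The share wanted is P(G > 0 and P ≤ 0) / P(G > 0).

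- For m = 0 this is [1/4 − arcsin(r)/(2π)] / 0.5.
- For m = −0.35 (both improve by 0.35 SD), P(G > 0) = Φ(−0.35) = 0.363, and the joint probability comes from the bivariate normal.

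| r | m = 0: joint probability, share | m = −0.35: joint probability, share |
|---|---|---|
| 0.3 | 0.202, 40% | 0.188, 52% |
| 0.5 | 0.167, 33% | 0.156, 43% |
| 0.7 | 0.127, 25% | 0.119, 33% |

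The Sample Size Calculation section gives 300 randomised 1:1 with 20% dropout, so 300 × 0.8 / 2 = 120 completers per arm. Multiplying by the joint probabilities gives 0.119 × 120 ≈ 14 to 0.202 × 120 ≈ 24 youth per arm with some rise in anxiety and no rise in PHQ-9. The model counts any rise, however small, so part of this is measurement noise. Requiring a larger rise in anxiety would change the numbers.

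**3. Single items: a sum can hide a worsening item**

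Take nine items (the item count and 0 to 3 scoring are assumed; the article does not describe them). Before: eight items at 1 and one at 0, total 8. After: five at 1, three at 0 and one at 3, total 5 + 0 + 3 = 8. One item has risen by 3 and the total has not moved.

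To illustrate with assumed values, let one item rise by 1 and let the sum of the others change with mean μ and SD 4.5. The total does not rise if the others change by −1 or less, with probability Φ((−0.5 − μ)/4.5):

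- μ = −1: Φ(0.11) = 0.54
- μ = +2: Φ(−0.56) = 0.29
- μ = +3: Φ(−0.78) = 0.22

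A stricter cut-off on the total does not help. If a 5-point rise were required (the plan has no such cut-off), the miss at μ = +2 would be Φ((3.5 − 2)/4.5) = Φ(0.33) = 0.63.

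**The case against.** **Anxiety is already compared between arms.** It is a predefined secondary outcome, and an intention-to-treat analysis of the offer is planned. A reader might infer from the safety sentence that the trial could miss a general rise in anxiety in the offered arm. The documents do not support that: a mean worsening would show in the secondary outcome. What remains is narrower. A comparison of scores can show no mean difference while some youth worsen and others improve. The article itself chose a proportion-deteriorated measure for safety, and anxiety has none.

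**The PHQ-9 is not the sole source on safety.** The interviews address perceived safety and are to be integrated with the trial data. That stands, and it limits the point to the quantitative endpoint. The interviews are small and confined to exposed youth, so they give no control-arm comparison.

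**Suicidal thoughts.** A reader might infer that worsening suicidal thoughts would be hidden in the total. Nothing in the article describes the content of the PHQ-9 items, and the survey was adapted after piloting. That part therefore depends on the sponsor confirming what was fielded. The anxiety part does not.

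**This is a condensed article.** Supplementary tabulations are ordinary content for a full protocol or analysis plan, and their absence here would be no fault. But the safety sentence is a stated rule, not a gap: it says what will count as deterioration and restricts it to the PHQ-9.

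**The inputs are guesses.** The percentages above are illustrations, not estimates for this trial. This stands in full.

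**Conclusion.** The point holds for the quantitative safety endpoint. As defined, it counts individual harm only when the PHQ-9 rises, and no other planned analysis in the article counts, by arm, youth who deteriorated in anxiety, flourishing or somatic symptoms. The article contradicts nothing by this; the choice is coherent but narrower than objective 5 and the Background call for, and worth correcting because the data will already exist.

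The size cannot be derived from the documents. On the assumptions shown, between a quarter and a half of youth with any rise in anxiety would not be flagged, with the larger share when both scores improve on average.

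The conclusion rests on two readings. The first is that scores in the safety sentence means the total, which is an inference from the article's use of the term elsewhere. The second is that the surveys are given unchanged to both arms, which the data collection section implies. The suicidal-thoughts part is conditional on the item being in the fielded survey.

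**What to change.** In the Data Analysis section, replace the safety sentence with a statement that safety will be reported by randomised arm as:

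- (a) the proportion with deterioration on the PHQ-9 total;
- (b) the proportion with individual deterioration on the Generalized Anxiety Disorder scale from the 6-month to the 18-month survey, with the Flourishing Scale and the somatic symptoms inventory as supportive;
- (c) if the sponsor confirms that the fielded PHQ-9 includes a suicidal-thoughts item, the proportion with a new or higher score on it.

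State in advance what counts as deterioration on each scale. Limit the safety conclusion to the domains measured. Posttraumatic stress, for example, is named in the Background, but no scale for it is listed in the Measurement Tools section.

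The cost is a few extra rows in the safety table, with no new visits, participants or instruments. Counts will be small and intervals wide. With 120 completers per arm and an assumed true proportion p in both arms, the 95% half-width of the difference is 1.96 × √(2p(1 − p)/120): about 5.5 percentage points at p = 0.05, 7.6 at 0.10 and 10.1 at 0.20. These results should therefore be read as descriptive, with intervals, and not as proof that harm is absent.
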